# Remote Ischemic Conditioning for Intracerebral Hemorrhage (RICH-1): Rationale and Study Protocol for a Pilot Open-Label Randomized Controlled Trial

**DOI:** 10.3389/fneur.2020.00313

**Published:** 2020-04-28

**Keywords:** intracerebral hemorrhage, hematoma resolution, remote ischemic conditioning, randomized controlled trial, safety

## Abstract

**Background and rationale:** Although many therapies have been investigated for intracerebral hemorrhage (ICH), none have succeeded in improving the functional outcomes. Remote ischemic conditioning (RIC) has been proven to promote hematoma resolution and improve neurological outcomes in an ICH model; whether it is safe and feasible in patients with ICH remains unknown. This trial aims to assess the safety, feasibility, and preliminary efficacy of RIC in patients with ICH and to plan for a phase-2 study.

**Methods:** A proof-of-concept, assessor-blinded, pilot open-label randomized controlled trial will be carried out with patients with ICH within 24–48 h of ictus. All participants will be randomly allocated to the intervention group and the control group with a 1:1 ratio (*n* = 20) and will be treated with standard managements according to the guidelines. Participants allocated to the intervention group will receive RIC once daily for 7 consecutive days. Cranial computed tomography examinations will be performed at baseline, and on days 3, 7, and 14. Neurological outcomes will be assessed at baseline, and on days 1 to 14, 30, and 90. The primary outcome to be tested is safety. Secondary tested outcomes include changes of hematoma and perihematomal edema volume, incidence of hematoma expansion, functional outcomes, and frequency of adverse events.

**Discussions:** This study will be the first proof-of-concept randomized controlled trial to ascertain the safety, feasibility, and preliminary efficacy of RIC in patients with ICH, results of which will provide parameters for future studies and provide insights into the treatment of ICH.

**Trial Registration:**
Clinicaltrials.gov, identifier: NCT03930940.

## Introduction and Rationale

Intracerebral hemorrhage (ICH) is a severe neurological disease and public health issue that accounts for 10–15% of strokes in European and American countries and 20–30% of strokes in Asian countries (1, 2). Although the rate of ICH is far lower than that of ischemic stroke, which is more than 70% of all strokes, its mortality is as high as 50% at 30 days. Furthermore, only 20% of survivors regain functional independence (2). Over recent decades, many corresponding strategies, such as invasive and minimally-invasive hematoma evacuation, blood pressure control, hemostatic therapy, and osmotic treatment, have been investigated; however, few of them have succeeded in improving functional outcomes (3), leading ICH to be the least treatable type of stroke (4), and novel strategies and approaches for the treatment of ICH are urgently needed.

Remote ischemic conditioning (RIC) is a noninvasive systemic protective strategy in which several cycles of brief focal ischemia followed by reperfusion in arms or legs confer protection against more severe injuries in distant organs (5). At present, RIC if applied in arms has been found to benefit patients with acute ischemic stroke, intracranial atherosclerotic stenosis, cerebral small vessel disease, and those undergoing carotid stenting (6–9). Although the underlying mechanisms are not fully understood, current evidence indicates that RIC could reduce inflammation, oxidative stress, and cerebral edema and have other positive impacts (10, 11). Furthermore, in critically ill patients with aneurysmal subarachnoid hemorrhage, RIC applied in the legs has been demonstrated to be feasible, safe, and well-tolerated, with the potential to prevent delayed cerebral artery spasm and to reduce the incidence of both stroke and death (12–14).

In the ICH model, RIC has been found to reduce cerebral edema without exacerbating hematoma size within 72 h of ictus (15, 16). More recently, an experimental study further demonstrated that 6 consecutive days of RIC could improve local cerebral blood flow perfusion, promote hematoma resolution, and improve neurological outcomes (17). However, it remains unknown whether RIC is safe, feasible, and effective in human patients with ICH.

We therefore designed the Remote Ischemic Conditioning for intracerebral Hemorrhage (RICH) study to investigate the safety, feasibility, and efficacy of RIC performed in unilateral arm in patients with ICH. RICH-1 is a pilot study, aiming to determine the safety and feasibility of RIC in patients with ICH and to plan for a prospective phase-2 study (RICH-2) that will investigate the efficacy of RIC.

## Methods

### Study Design

This is a proof-of-concept, assessor-blinded, pilot open-label randomized controlled trial that will be carried out in four centers with patients who suffered from ICH and will receive nonoperative treatment. The trial design flowchart is illustrated in Figure 1. Participants meeting the inclusion criteria but not the exclusion criteria will be randomly allocated to the RIC group or the control group. Both groups will be treated with the standard management according to the guidelines (4). Remote ischemic conditioning will be performed in the RIC group for 7 consecutive days after enrollment. Cranial computed tomography (CT) examination will be performed at baseline and days 3, 7, and 14. The National Institutes of Health Stroke Scale (NIHSS) score will be assessed by trained investigators blinded to the treatment assignment at baseline and days 1–14 after enrollment. Modified Rankin Scale (mRS) will be evaluated by trained investigators blinded at days 30 and 90.

**Figure 1 F1:**
[figure not shown]
Trial design flowchart. ICH, intracerebral hemorrhage; GCS, Glasgow Coma Scale score; RIC, remote ischemic conditioning; NIHSS, National Institutes of Health Stroke Scale; mRS, modified Rankin Scale; CT, computed tomography.

All participants will be informed about the clinical study and the requirements to give informed consent. This study was approved by the ethical committee of each center and has been registered at *Clinicaltrials.gov* with NCT03930940.

### Patient Population: Inclusion and Exclusion Criteria

Participants will be recruited from the wards. The inclusion criteria are (1) ≥18 and ≤80 years old; (2) diagnosis of supratentorial ICH confirmed by brain CT scan; (3) hematoma volume of 10–30 mL; (4) Glasgow Coma Scale (GCS) score >8; (5) ability to start RIC treatment within 24–48 h of ictus; and (6) informed consent provided by participant or legally authorized representative.

Exclusion criteria are as follows: (1) patients with suspected ICH secondary to tumor, coagulopathy, ruptured aneurysm or arteriovenous malformation, venous sinus thrombosis, cerebral infarction, and traumatic brain injury; (2) ICH concomitant with subarachnoid hemorrhage or intraventricular hemorrhage and planned surgical evacuation for the index hematoma prior to enrollment; (3) evidence of significant shift of midline brain structure (>10 mm) or herniation on brain imaging; (4) known pregnancy or breastfeeding; (5) concurrent participation in another research protocol investigating a different experimental therapy; (6) preexisting neurological deficit (mRS score >1) or psychiatric disease that would confound the neurological or functional evaluations; (7) life expectancy of fewer than 90 days due to comorbid conditions; (8) severe hepatic and renal dysfunction; (9) severe, sustained hypertension (systolic blood pressure >180 mm Hg or diastolic blood pressure >110 mm Hg); (10) contraindication to RIC because of severe soft tissue injury, fracture, or peripheral vascular disease in the upper limbs; (11) any condition which, in the judgment of the investigator, might increase the risk to the patient.

### Randomization

All enrolled participants will be randomly assigned in a 1:1 ratio to the RIC group and the control group (*n* = 20 each). The randomization sequence will be made according to a predefined table generated by a computer program. Subsequently, the randomization sequence that indicated the group allocation will be concealed in sequentially numbered opaque closed envelopes. A research assistant, who will not be involved in the study, will prepare the envelopes prior to the study. After recording baselines measures, participants will be randomly allocated to either the RIC or the control group by the treating physicians who will open the sealed opaque envelopes.

### Interventions

Participants in both groups will receive the standard management according to the guidelines, including blood pressure control, interventions for elevated intracranial pressure and mass effect, treatment of seizures, prevention of venous thromboembolism, maintenance of fluids, treatment of hyperglycemia, rehabilitation, and so on. In addition, participants allocated to the RIC group will undergo the RIC procedure once daily for 7 consecutive days after enrollment, and the interval between two RIC procedure is 24 h. In all the centers, the RIC procedure will be induced by using the same electric autocontrol device with cuffs placed on the nonaffected arm (Figure 2) and will consist of four cycles of arm ischemia with cuffs inflated to a pressure of 200 mm Hg for 5 min followed by reperfusion for another 5 min. The RIC procedure will be performed with assistance from a hospital-based nurse. For participants allocated to the control group, no RIC will be received.

**Figure 2 F2:**
[figure not shown]
The remote ischemic conditioning device and how it is used. **(A)** The device used for stimulating remote ischemic conditioning. **(B)** Remote ischemic condition performed in human, the device can be used on both sides or one side according to the requirements of the study.

### Outcomes

#### Safety Outcomes Assessment

The safety is defined as any of the following: (1) neurological deterioration defined as an increase of four or more points in the NIHSS or a decrease of two or more points in the GCS score within 7 days of enrollment without a clear explanation; (2) death during the study period regardless of cause; (3) any adverse event that prolongs hospitalizations or requires medical treatment during the study period.

### Data Monitoring

Database management and statistical analyses will be performed by an independent investigator blinded to the treatment assignment of this study. The treatment physicians will monitor compliance with training.

### Sample Size Estimation

When estimating the sample size, no parameters could be referred to, as there is no completed clinical study of RIC in patients with ICH. Fortunately, Dobkin (20) has shown that 15 patients per group are often adequate for determining whether a larger multicenter trial should be conducted. Furthermore, Hertzog (21) has suggested that 10 to 20 patients in each research group are sufficient to evaluate feasibility in a pilot study. Therefore, our goal is to recruit 20 patients in each group. Results of this study should be able to determine the preliminary safety and feasibility of RIC in patients with ICH and will be used to estimate sample size and conduct a power calculation to plan a phase-2 trial.

### Statistical Analyses

All analyses will be done according to the intention-to-treat principle, which will include all participants who enrolled in this trial. Per-protocol analyses, excluding patients who fail to complete the follow-up, will be managed as a supplement of the intention-to-treat analysis to further confirm the results. If the between-group difference in the change of hematoma volume at day 7 is not <12% in favor of RIC, we would move forward with a phase-2 trial.

Categorical variables including the incidence of hematoma expansion, the proportion of good functional outcomes, and the frequency of adverse events will be presented as counts and percentages. These will then be analyzed with χ^2^ test, Fisher exact test, or continuity correction where appropriate. Continuous variables including NIHSS score, GCS score, and hematoma and perihematomal edema volume will be presented as mean and standard deviation or median and interquartile range. These will be analyzed with independent *t-*test or rank-sum test where appropriate. For missing data, we will conduct a sensitivity analysis and use multiple imputations to impute values for those with missing data as continuous data; for clinical events (e.g., death), we will regard the patients lost to follow-up as nonevents in both groups.

The statistical analyses will be conducted with SPSS statistics software for Windows version 20.0 (Armonk, NY, IBM Inc.).

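### Safety is the primary outcome, but the only inference stated for it is a between-arm test of no difference, which at 20 per arm cannot support the preliminary safety determination the protocol promises

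*Protocol article*

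**What the plan says.** The Abstract of the protocol article states: "The primary outcome to be tested is safety". Safety Outcomes Assessment defines it as the occurrence of any of three things: unexplained neurological deterioration within 7 days, death from any cause, or "any adverse event that prolongs hospitalizations or requires medical treatment during the study period". This gives a yes/no outcome for each patient.

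Sample Size Estimation sets the size ("our goal is to recruit 20 patients in each group") from rules of thumb for pilot studies, explaining that "no parameters could be referred to". It then says: "Results of this study should be able to determine the preliminary safety and feasibility of RIC in patients with ICH". The Discussion repeats the aim without the word preliminary: safety and feasibility will be determined.

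Statistical Analyses says that categorical variables, with adverse event frequency among the examples, "will be presented as counts and percentages". They are then compared between arms by χ² test, "Fisher exact test, or continuity correction where appropriate". That section names no interval estimate, margin or acceptable event rate for safety.

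**The concern.** A test of no difference puts the burden of proof on harm: unless the arms differ enough, the result is non-significant. In a small trial that is the default outcome, whether or not remote ischemic conditioning (RIC) does some harm. The method therefore does not match the question. The protocol wants to say something about how safe RIC is, but its inference can only say whether a difference has been demonstrated.

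What is at stake is how the primary result will be read. If the headline is a comparison with a p-value above 0.05, readers may take it as reassurance that 40 patients cannot give. The trial is meant to inform the planning of a phase-2 study, so a clear statement of what the safety data do and do not exclude matters.

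**Working it through.** **Plan's own figure.** The size of 20 per arm rests on cited rules of thumb (15 per group; 10 to 20 per group). There is no formula to reproduce, and no power for safety is claimed.

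**Inputs from the protocol article.** n = 20 per arm (Sample Size Estimation); patients "randomly assigned in a 1:1 ratio to the RIC group and the control group" (Randomization); binary safety outcome (Safety Outcomes Assessment); χ², Fisher or continuity-corrected test (Statistical Analyses).

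**Assumptions.** The documents give neither a significance level nor safety event rates. I take a two-sided 5% level and a range of rates.

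**Step 1: power of the stated tests.** Let X (RIC) and Y (control) be independent binomials with n = 20. Power = Σ over all x, y from 0 to 20 of P(X = x) · P(Y = y) · 1[p-value(x, y) < 0.05], by full enumeration.

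| Control v RIC, true rate | Fisher | χ², uncorrected |
|---|---|---|
| 5% v 10% | 1.7% | 5.4% |
| 10% v 20% | 7.2% | 13.8% |
| 10% v 30% | 24.2% | 35.7% |
| 10% v 40% | 49.2% | 62.3% |
| 10% v 50% | 74.2% | 83.8% |
| 20% v 40% | 19.2% | 29.1% |
| 20% v 60% | 65.0% | 75.3% |
| 50% v 70% | 16.3% | 24.5% |

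A doubling from 10% is missed in 100 − 7.2 = 92.8% of trials by Fisher and in 100 − 13.8 = 86.2% by uncorrected χ². The continuity-corrected test has lower power than Fisher in every case examined.

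**Step 2: what it takes to reach significance.** With 2/20 control patients having an event, Fisher needs 9/20 in the RIC arm (p = 0.031); 8/20 gives p = 0.065. With 4/20 in control it needs 11/20 (p = 0.048).

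**Step 3: what a non-significant result leaves open.** Take 6/20 on RIC and 2/20 on control: difference 0.30 − 0.10 = +20 points, Fisher p = 0.235. The Wilson 95% intervals are 0.146 to 0.519 and 0.028 to 0.301. The Newcombe limits are:
- lower: 0.20 − √[(0.300 − 0.146)² + (0.301 − 0.100)²] = −0.054
- upper: 0.20 + √[(0.519 − 0.300)² + (0.100 − 0.028)²] = +0.431

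So a result that passes as no significant difference is compatible with an excess of 43 points.

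**Step 4: precision available if safety is estimated.**
- No events in 20: exact (Clopper-Pearson) upper 95% limit = 1 − 0.025^(1/20) = 16.8%.
- 2/20: 1.2% to 31.7%. 4/20: 5.7% to 43.7%.
- Equal counts of 4/20 in both arms: Wilson 0.081 to 0.416 each, so Newcombe 0 ± √[(0.200 − 0.081)² + (0.416 − 0.200)²] = about −25 to +25 points.

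**The case against.** The strongest case on the other side has five parts.

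- **Counts and percentages are reported too.** This stands. They are central to a pilot safety review, and any interval can be computed from them. It would be wrong to say that safety is addressed by significance tests alone. The tests are only the sole inference stated.
- **The power figures depend on assumed rates.** This stands. A reader might infer that the tests will almost never be significant, or that any tripling of risk will usually be missed. The numbers do not support either: 20% v 60% has 65% Fisher power and 10% v 50% has 74%. The composite is broad, so its event rate could be well above 10%, and 0/20 may be an unlikely result. The statement is therefore limited to modest to moderate harm.
- **The promise is modest.** Sample Size Estimation says preliminary and claims no power. This stands, and low power in such a pilot is not itself an error. The Discussion is worded more strongly, however, and even a preliminary conclusion needs a method that bears on it.
- **No safety p-value drives the phase-2 decision.** A reader might infer that a non-significant safety test would trigger phase 2. The text does not say so: the only stated go rule uses hematoma volume at day 7. Nor does the article say that non-significance will be read as safe.
- **Intervals may be in an analysis plan that is not shown.** They may, and their absence here is not the point. The categorical list is also introduced as examples and names neither the composite nor death. But the article fixes a method of inference for categorical outcomes and states what the trial will determine, and those two do not fit together.

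**Conclusion.** The point holds in a limited form. The primary question is safety, the only stated inference for a categorical outcome is a test of no difference, and at 20 per arm that test cannot support even a preliminary safety conclusion. Under a doubling of risk from 10% or 20%, power is 7% to 29%, depending on the starting rate and on whether Fisher or uncorrected χ² is used. For 10% v 30% it is 24% to 36%. Very large harm would often be detected. These figures rest on an assumed two-sided 5% level and assumed event rates, on all 40 patients being evaluable, and on the safety outcome being analysed by the methods given for categorical variables. The logical mismatch between a difference test and a safety conclusion does not depend on the rates. This is neither a call for a larger trial nor a claim that the go rule misuses the safety test.

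**What to change.** 1. In Statistical Analyses, make estimation the primary safety analysis. Give the proportion of patients with any event under Safety Outcomes Assessment in each arm with an exact 95% interval, and the risk difference with a Newcombe 95% interval. The tests can stay as supporting output.
2. State that a non-significant p-value will not be read as evidence of safety, and that the safety conclusion will be drawn from the upper limits of the intervals.
3. In Sample Size Estimation, replace the claim about determining safety with the precision available: for example, 0/20 excludes only event rates above about 17%, and 4/20 in both arms leaves a difference of about −25 to +25 points open. Align the Discussion with it.

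The cost is a change of wording and a few lines of output from data already collected. Sample size, visits and assessments do not change. The downside is that the safety claim becomes more modest.

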## Discussion

Recently, the Minimally Invasive Surgery Plus Alteplase for Intracerebral Hemorrhage Evacuation III trial that evaluated the efficacy of minimally invasive evacuation followed by thrombolysis in ICH patients has completed, but it failed to improve functional outcomes despite a significantly decreased hematoma volume (22). Therefore, exogenous removal of hematoma may not be as effective as expected. Fortunately, the Intracerebral Haemorrhage Deferoxamine trial found that deferoxamine was safe in patients with ICH and merited further investigation in a phase 3 trial (23). Therefore, strategies that promote hematoma resolution and inhibit the secondary injury of hematoma appear to be promising in the future.

Remote ischemic conditioning has been found to attenuate perihematomal edema, improve cerebral blood flow, and promote hematoma resolution in ICH model (15, 17). In this study, the safety and feasibility of RIC will be determined, and cranial CT will be performed at days 3, 7, and 14 to ascertain the potential effects of RIC on hematoma resolution and perihematomal edema, which will provide parameters for the design of a phase-2 study. Approximately 40% of patients experience hematoma expansion over the first 24 h after ictus (19), which further exacerbates the damage from ICH and is associated with neurological deterioration and worse outcomes (24). In this study, we exclude patients within 24 h of ictus and recruit patients at 24 to 48 h. One reason for this is to ensure safe implementation of the present study. Another reason is that the aim of the RICH trial is to evaluate the effects of RIC on hematoma resolution and edema instead of hematoma expansion. In addition, two other ongoing clinical trials (RESIST, NCT 03481777; SERIC-sICH, NCT03484936) are recruiting ICH patients within 4 and 12 h of ictus respectively and evaluating the effects of RIC on hematoma expansion.

There are limitations to this study. First, the RIC dose that will be used in this study is rather pragmatic and tailored to ICH patients, but it may not be the optimal one. In addition, a sham procedure is not planned in this study, and the participants will be not blinded; this may bias the study results. To alleviate potential bias, all outcomes raters will be blinded to the treatment assignment of this study.

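### Counting patients lost to follow-up as event-free understates event rates in the primary safety outcome and can distort the comparison between arms

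*Protocol article*

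**What the plan says.** The Abstract of the protocol article sets the priority: "The primary outcome to be tested is safety". Safety Outcomes Assessment gives three components:

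- neurological deterioration, limited to the period "within 7 days of enrollment without a clear explanation";
- "death during the study period regardless of cause";
- "any adverse event that prolongs hospitalizations or requires medical treatment during the study period".

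Follow-up runs to day 90 (Study Design: "Modified Rankin Scale (mRS) will be evaluated by trained investigators blinded at days 30 and 90"). The target is 20 patients per arm (Sample Size Estimation: "Therefore, our goal is to recruit 20 patients in each group").

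The Statistical Analyses section then fixes the handling of missing events: "for clinical events (e.g., death), we will regard the patients lost to follow-up as nonevents in both groups". The same section plans multiple imputation for continuous data, a sensitivity analysis for missing data whose content is not given, and a supplementary analysis without patients who did not complete follow-up. The Discussion concedes that "a sham procedure is not planned in this study, and the participants will be not blinded".

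**The concern.** The rule is a single imputation of the best possible value, applied to the outcome the trial exists to assess. Death, its own example, is a component of that outcome. Two of the three components run to the end of the study, so a patient who disappears between discharge and day 90 can have an event that nobody records and is then analyzed as event-free.

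Two things are at stake. One is the event rate in each arm, which is the main product of a pilot safety study and will inform the planning of phase 2. The other is the comparison between arms. RIC is an extra procedure given openly in one arm only, so loss may differ between arms, and the rule then treats the arms unequally although its wording is symmetric.

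**Working it through.** **Inputs.** From the article: 20 per arm, the nonevent rule, and the three safety components. The article gives no event rate for this population and no expected loss. All rates and loss counts below are therefore assumptions. The sample size rests on pilot-study rules of thumb, so there is no planned figure to reproduce.

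**1. Bias within an arm.** Let d be the fraction lost, p the event rate among those followed, and q the rate of unrecorded events among those lost.

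- True rate = (1 − d)p + dq
- Rate under the rule = (1 − d)p
- Shortfall = dq, which is never negative

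| Loss (of 20) | Rule reports, p = 20% | True, q = 20% | True, q = 40% |
|---|---|---|---|
| 5% (1) | 19% | 20% | 21% |
| 10% (2) | 18% | 20% | 22% |
| 20% (4) | 16% | 20% | 24% |

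One lost patient moves an arm's rate by at most 1/20 = 5 points.

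**2. Similar loss in both arms, q = p within each arm.** Every rate is multiplied by (1 − d). For true rates of 30% and 10%:

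- The risk difference falls from 20 points to 19, 18 and 16 at 5%, 10% and 20% loss.
- The risk ratio stays at 3.0, because (1 − d) cancels.
- Approximate power (two-sided 5%, assumed) falls from 35% to 33%, 31% and 28%.

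**3. Unequal loss, q = p.**

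- True rate 20% in both arms, 20% loss on RIC only: 0.20 × 0.80 − 0.20 = −0.04. RIC falsely looks 4 points safer (risk ratio 0.80).
- The same loss in control only: 0.20 − 0.20 × 0.80 = +0.04. RIC falsely looks harmful (risk ratio 1.25).
- True rates 25% (RIC) and 20% (control), 20% loss in control only: 0.25 − 0.16 = 0.09. The difference grows from 5 to 9 points.

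The rule can therefore create, hide or enlarge a difference.

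**4. Example with counts.** Assume 2 events seen in each arm, 3 other RIC patients lost with no event recorded, and no controls lost.

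| Handling | RIC rate | 95% CI (exact) | Fisher p against control 2/20 |
|---|---|---|---|
| Nonevent rule | 2/20 = 10.0% | 1.2% to 31.7% | 1.00 |
| Known status only | 2/17 = 11.8% | 1.5% to 36.4% | 1.00 |
| All lost RIC patients had events | 5/20 = 25.0% | 8.7% to 49.1% | 0.41 |

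The data are compatible with any RIC rate from 10% to 25%. The rule reports the lowest.

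**5. Effect of events already recorded before loss.** Take true rates of 30% and 15%, with 4 RIC patients and 1 control lost.

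- All events in lost patients unseen: (16 × 0.30)/20 − (19 × 0.15)/20 = 0.24 − 0.1425 = 9.75 points instead of 15, an attenuation of 35%.
- Two-thirds of those events recorded before loss (assumed): RIC (4.8 + 4 × 0.30 × 2/3)/20 = 28.0%; control (2.85 + 1 × 0.15 × 2/3)/20 = 14.75%. The difference is 13.25 points, an attenuation of 12%.

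**The case against.** **The loss may be small, and most events early.** Neurological deterioration is confined to the first 7 days, NIHSS is scored to day 14, and RIC is given with a hospital-based nurse. On the natural reading, events recorded before loss still count and only unknown later status becomes a nonevent. This stands. Step 5 shows that it can cut the attenuation from 35% to 12%. The standard error of that risk difference is itself about 13 points: √(0.30 × 0.70/20 + 0.15 × 0.85/20) = 0.130. What remains is deaths and adverse events after contact is lost.

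**The plan has other analyses.** The completers-only supplement is close to an observed-case check, and a sensitivity analysis is promised. This stands in part. The supplement assumes that lost patients resemble those followed, and the article does not say whether patients who died count as completers. The sensitivity analysis has no stated content for events. Neither bounds the unknown outcomes.

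**No decision hangs on it.** The article states no safety threshold, and its one stated criterion for moving to phase 2 is the day-7 hematoma change, which the rule does not touch. That is correct and limits the consequence. The reported safety result is still affected.

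**Stronger readings that the article does not support.** A reader might infer that the rule always pulls toward no difference. It does so for the risk difference under step 2's conditions; the risk ratio is then unchanged, and step 3 shows movement either way. A reader might infer that it favors RIC. Nothing in the article says that loss will be heavier on RIC. A reader might also extend the rule to the 90-day mRS proportion, so that a lost patient counts as a poor functional outcome. The article lists that proportion separately and does not apply the rule to it.

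**Conclusion.** The concern holds in this form. As written, the rule understates an arm's rate of death or adverse events whenever a lost patient had an unrecorded event, and it can never overstate that rate. Its effect on the comparison depends on the pattern of loss. The risk difference shrinks when loss is similar and lost patients carry the same risk as those followed in their arm; the bias has no fixed direction when loss is unequal.

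The size cannot be derived from the article. On the assumed rates the shortfall is 1 to 8 points per arm for 1 to 4 of 20 patients lost. In the count example the RIC rate lies between 10% and 25% and is reported as 10%. These figures treat all events in lost patients as unrecorded, so they are upper-end illustrations; early recording of events makes the effect smaller. With no loss to follow-up the rule does nothing.

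**What to change.** Remove the nonevent rule as the only handling of missing clinical events, and state instead:

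1. Every event recorded before loss counts, whatever happens later.
2. The number lost, and the time of last contact, are reported by arm.
3. The safety outcome is presented on patients with known status; for death, time to event with censoring at last contact is an alternative.
4. Two bounds on all enrolled patients accompany it: lost RIC patients as events with lost controls as nonevents, and the reverse.
5. A tipping-point count gives the number of lost patients who would need to have had an event for the safety conclusion to change.

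The bounds keep everyone in the denominator and so respect the intention-to-treat statement. The known-status analysis does not, and it too is biased if loss is related to outcome, so the two belong together.

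The cost is analysis wording only, with no change to conduct or sample size. The downside is slightly wider intervals and less favorable reported event rates. In the count example, the known-status RIC result moves from 10.0% (1.2% to 31.7%) to 11.8% (1.5% to 36.4%).
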